### 2.3. Inclusion Criteria 

Men and women between 20 and 65 years of age, who failed to meet the recommended 150 minutes of moderate PA [2] per week, were eligible for the study. Additionally, individuals had to understand German sufficiently in order to complete the study procedures. They also had to have residence in Switzerland. Inclusion criteria were checked using a questionnaire sent by e-mail. Physical activities of the previous week were assessed by an adapted version of the Simple Physical Activity Questionnaire (SIMPAQ [40]). Participants were further screened using the Physical Activity Readiness Questionnaire (PAR-Q [41]). Individuals who reported one or more health concerns in the PAR-Q were asked to consult their general practitioner (GP). If their GP approved moderate PA, individuals were deemed eligible. Individuals who reported more than 150 minutes of moderate PA or who shared the same household with another study participant were excluded. Further exclusion criteria were current pregnancy or a planned absence of more than 3 weeks during the next 6 months. 

### 2.4. Group Allocation

A computer-based minimization procedure [42] stratified by age and sex was used to assign participants randomly to one of the three study arms. The randomization was conducted by a member of the research team, who was not involved in the intervention. In order to simplify the allocation of participants within the study team, randomization occurred prior to baseline data collection. Neither the study team nor the participant knew the group allocation prior to the start of the intervention.

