## Abstract

*Background*. Physical inactivity is currently seen as one of the biggest global public health issue. Remote physical activity (PA) promotion programs are expected to be effective if they are individually tailored and include behavior change techniques, personal coaching, and regular prompting. However, it is still not fully understood which intervention components are most effective. This paper describes the rationale and design of a study on an individually tailored remote PA promotion program comparing the efficacy of coaching and prompting with a single written advice. *Methods*. In total, 288 adults (age 20 to 65 years) were randomly assigned to three different intervention arms of a 6-month-long PA promotion program. A minimal intervention group received a single written PA recommendation. The two remaining groups either received telephone coaching sessions (*n* = 12 calls) with or without additional short message service (SMS) prompting (*n* = 48 SMSs for each participant). Data assessment took place at baseline, at the end of the intervention, and after a six-month follow-up-period. The primary outcome of the study was self-reported PA. Objectively assessed PA, psychosocial determinants of PA, well-being, body mass index (BMI), and adherence were assessed as secondary outcomes. *Conclusion*. Findings of this three-arm study will provide insight into the short and long-term effects of coaching and prompting for PA promotion.

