### 2.2. Recruitment and Sample Size 

Participants were recruited through newspaper advertisements, e-mail newsletters, advertisements provided by local and cantonal administration offices, companies’ communications to employees, and flyers in pharmacies, medical practices, and physiotherapy clinics, as well as by word-of-mouth publicity. Individuals who were interested in participating contacted the study team by e-mail or by phone. Eligible individuals were provided with a written informed consent before participating in the study.

Based on previous studies on remote PA promotion and the comparison of SMS prompts with alternative interventions [8,20] a small effect (d = 0.21) on self-reported PA was expected. Based on this expectation, a sample size calculation for an analysis of covariance (ANCOVA) including baseline PA as a covariate was computed [39]. In order to achieve a power of at least 80% (1-β error probability) and a significance level of 5%, a total of 242 participants were required. A subsequent total sample size of approximately 284 participants was needed after adjusting for an expected dropout rate of 15–20%.

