### 2.7. Assessment of Primary and Secondary Outcomes

The assessment of primary and secondary outcomes is conducted without on-site presence of participants. Self-reported and objectively assessed PA level of one week, theoretical domains of PA as well as health and wellbeing-related variables are assessed in the pre, post and follow-up tests. After 3 months of intervention all participants are asked to answer a feedback questionnaire. Personal data and socio-demographic information are assessed during the inclusion procedure. Measures of all test periods are displayed in Table 4.

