### 2.8. Data Processing and Statistical Analysis

ActiGraph data are analyzed using the ActiLife software (Version 6.13.3, ActiGraph, Pensacola, USA). Daily minutes of moderate-to-vigorous physical activity (MVPA) are computed after declaring sleep and non-wear time. Currently there are no widely used and validated cut-off-values to classify MVPA for adults’ activity count of wrist-worn ActiGraph data. The cut-off values are therefore chosen on the basis of existing explorative analysis [77] and their comparison to cut-off points for children [78]. According to Kamada et al. [77] activity counts per minute are classified as sedentary activity 0–1999, light activity 2000–8249, and MVPA > 8249. The option “worn on the wrist” provided by the ActiLife software is not selected given its systematic underestimation of energy expenditure [79]. Sleep is determined using the Cole–Kripke algorithm [80]. Non-wear time is calculated according to Troiano [81]. Physical activities listed on the non-wear sheet (e.g., swimming) are added as moderate activities. In order to be analyzed, participants need to have a non-wear time of less than 10% [82]. At least four weekdays and one weekend day are required [55]. The first day of wear-time is not included. For further analysis, the mean of MVPA per day of all assessed valid days is computed.

All statistical analysis will be conducted as intention-to-treat. Group differences in primary and secondary outcomes will be calculated using linear mixed models. Linear mixed models will include intervention group, time, group × time interaction, and baseline measures as fixed effects and subjects as random effects. Statistical analysis will be conducted using the statistical software STATA (StataCorp, College Station, USA). Effect sizes for pre-post change scores and the corresponding confidence intervals will be provided [83,84].

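### Age and sex drive the minimisation but are not named in the analysis model, which costs a little precision if they predict follow-up activity

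*Protocol article*

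**What the plan says.** Section 2.4 (Group Allocation) describes the method: "A computer-based minimization procedure [42] stratified by age and sex was used to assign participants randomly to one of the three study arms".

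Section 2.8 (Data Processing and Statistical Analysis) gives one model for primary and secondary outcomes: "Linear mixed models will include intervention group, time, group × time interaction, and baseline measures as fixed effects and subjects as random effects". Age and sex are not mentioned there, and no other section says that the minimisation factors enter an analysis.

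Section 2.2 (Recruitment and Sample Size) names a single covariate: "a sample size calculation for an analysis of covariance (ANCOVA) including baseline PA as a covariate was computed".

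Section 2.7 shows that the two variables are in hand from the start: "Personal data and socio-demographic information are assessed during the inclusion procedure".

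**The concern.** Minimisation makes the arms alike on age and sex, so these factors can add very little to the chance difference between arms. A model without them still counts the variance they explain as residual noise. Where the factors are prognostic, the reported SE describes a less balanced trial than the one that was run. Intervals come out too wide and tests reject less often than the nominal level under the null hypothesis.

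At stake is some precision in a trial that plans for a small difference ("a small effect (d = 0.21) on self-reported PA was expected"), and agreement between the way participants were allocated and the way their data are analysed.

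**Working it through.** **The plan's own figure.** Section 2.2 reaches a total of 242 from d = 0.21, 80% power and a 5% level. Taken as two-sided and without covariate adjustment, the number per arm is 2 × (1.960 + 0.842)² / 0.21² ≈ 356. The figure of 242 follows only with a baseline-to-follow-up correlation ρ that the article does not state. Setting 356 × (1 − ρ²) equal to 121 per arm (two arms) gives ρ ≈ 0.81. Setting it equal to about 81 per arm (three arms) gives ρ ≈ 0.88. So 242 cannot be reproduced from the stated inputs. The present point does not depend on it, and age and sex are not stated inputs to that calculation.

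**Inputs for the check**
- Balancing factors: age and sex (section 2.4).
- Model terms: group, time, group × time, baseline measures; subject as random effect (section 2.8).
- Reference design: 80% power at a 5% level (section 2.2; two-sided assumed).
- R², the share of outcome variance left after baseline PA that age and sex explain: not given in the article. Assumed to be 0, 0.02, 0.05 or 0.10.

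**Formulas.** Take the contrast between two arms at one follow-up, with the factors exactly balanced. The true variance of the difference is then (1 − R²) times the variance that the unadjusted model reports. Write s = √(1 − R²) and δ = 1.960 + 0.842 = 2.802, the standardised effect that gives 80% power when R² = 0.
- Reported SE / true SE = 1/s
- Type I error without age and sex = 2 × Φ(−1.960/s)
- Power without age and sex = Φ((δ − 1.960)/s)
- Power with age and sex = Φ(δ/s − 1.960)

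**Worked case, R² = 0.05.** s = √0.95 = 0.975. The SE ratio is 1/0.975 = 1.026. The type I error is 2 × Φ(−2.011) = 4.4%. Power without the factors is Φ(0.842/0.975) = 80.6%; with them it is Φ(2.874 − 1.960) = 82.0%.

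| Assumed R² | SE too large by | Type I error, factors omitted | Power, omitted | Power, adjusted | Difference (points) |
|---|---|---|---|---|---|
| 0 | 0% | 5.0% | 80.0% | 80.0% | 0 |
| 0.02 | 1.0% | 4.8% | 80.2% | 80.8% | 0.6 |
| 0.05 | 2.6% | 4.4% | 80.6% | 82.0% | 1.4 |
| 0.10 | 5.4% | 3.9% | 81.3% | 84.0% | 2.7 |

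**Simulation.** Exact balance is an idealisation, so three-arm minimisation was also simulated: 242 participants, three age bands and sex, an 80% biased coin, no dropout, 4,000 runs per R². These settings are assumptions, because the article does not describe the procedure further.
- At R² = 0.10 the mean model SE was 0.158 without the factors and 0.150 with them. Type I error was 3.4% against 4.7%, and power 81.4% against 84.3%.
- At R² = 0.05 type I error was 4.7% against 5.3%, and power 79.5% against 80.8%.

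The Monte Carlo standard error is about √(0.05 × 0.95/4000) = 0.3 points for type I error and √(0.8 × 0.2/4000) = 0.6 points for power. The simulation supports the direction and rough size of the formula results.

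**The case against.** **The wording may already cover it.** Section 2.8 says baseline measures without adding that these are measures of the outcome, and Table 4 lists socio-demographic data among the items taken at month 0. Age and sex are therefore not strictly excluded. This stands in part: they are unnamed rather than demonstrably left out. The narrower reading is still the natural one, because section 2.2 names baseline PA as the covariate and section 2.7 separates socio-demographic information from the outcomes measured repeatedly.

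**An article condenses.** A full covariate list could sit in a document that is not shown. That would settle the matter had the article been silent, but it lists the fixed effects, and the list does not match the allocation.

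**The harm is conditional.** This stands. Nothing in the article shows that age and sex predict follow-up PA once baseline PA is in the model. Dropout, expected at 15–20%, may also loosen the balance in the analysed set that the formula assumes.

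**Stronger readings that a reader might infer.** None of these is supported.
- That the group comparison is biased or the type I error inflated: the error moves the other way, towards conservative tests.
- That the trial loses its planned power: the only covariate named in that calculation is baseline PA, so omitting age and sex takes nothing from the 80%.
- That the benefit of minimisation is thrown away: even without adjustment, power rises from 80.0% to 81.3% as R² goes from 0 to 0.10. Only part of the gain is forgone.

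**Conclusion.** The point holds as a modest matter of efficiency and of coherence between design and analysis. The stated model does not name the factors used to balance the arms. For an assumed residual R² between 0.02 and 0.10, this makes SEs about 1% to 5% too large and leaves power about 0.6 to 2.7 points below what the same data would give with adjustment. With R² = 0 there is no loss.

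These sizes rest on the assumed R², on near-exact balance in the analysed participants, on a two-sided 5% test, and on a single follow-up contrast standing in for the full mixed model. The validity of the comparison is not in question. Whether 242 is adequate for d = 0.21 is a separate matter that does not bear on this point.

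**What to change.** Name age (in the form used for the minimisation, or as a continuous variable) and sex as fixed effects in the primary and secondary mixed models. If baseline measures was meant to include them, say so explicitly.

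The cost is one line of text and a few degrees of freedom: one for sex, and one for continuous age or one fewer than the number of age categories. Both variables are already collected at inclusion. Because the article describes the analysis in the future tense, the change can be recorded before outcomes are compared between arms, which also prevents a choice of covariates made after seeing results.

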### 2.5. Program Development

#### 2.5.1. Theoretical Foundation

The intervention content (e.g., BCTs) and delivery modes (e.g., frequency and density of participant’s contact) were defined according to the evidence of previous studies in the area of behavior change research and to theoretical considerations. 

The Behavior Change Wheel (BCW) framework [43,44] serves as the theoretical background of the intervention. The BCW allows a holistic consideration of behavior change interventions and summarizes existing behavior change theories. It clarifies the intervention functions (e.g., incentivization, training), policy levels (e.g., regulation, service provision), and BCTs which can influence behaviors. The theoretical domains framework of the BCW summarizes psychosocial determinants (e.g., social influences, beliefs about capabilities, goals) that explain the occurrence of a behavior in the so-called theoretical domains [45]. Each theoretical domain is influenced by certain BCTs [45]. Consequently, the selection of BCTs can be conducted theoretically by considering the theoretical domains. In contrast to various behavior theories, the BCW framework does not explain causal relations between the theoretical domains. Therefore, the MoVo (acronym for motivation and volition) Process Model by Fuchs et al. [46] serves as the theoretical basis to explain PA specific causal relations of theoretical domains. The MoVo Process Model combines concepts of stage theories (motivational and volitional phases of behavior change) and continuous behavior modes (causal relations). It represents an adaption of the Health Action Process Approach (HAPA) by Schwarzer [47] for PA-related behavior change. Psychosocial determinants of the MoVo Process Model are assessed as secondary outcomes (see Section 2.7.3) and used to tailor the intervention content individually (see Section 2.6.1).

#### 2.5.2. Intervention Content

The Movingcall program communicates BCTs and knowledge based on exercise science. The goal is to increase PA gradually and to reach the recommended 150 minutes of moderate PA per week or more [2]. Ten BCTs that were proven to be effective in changing PA behavior according to previous meta-analyses were selected (see background) [22,23,24,26,27,28,29,30,31]. For the present selection of BCTs, meta-analyses that defined BCTs according to an older taxonomy [48,49] were translated to the current V1 taxonomy. The resulting ten BCTs are described in Table 1. These BCTs were delivered to all participants.

The Movingcall program allows for 25 additional BCTs (listed Table 2). This includes BCTs that might be implemented unintentionally within the conditions of a regular coaching session (e.g., set graded tasks, focus on past success) and BCTs with scarcer evidence of effectiveness in previous studies (e.g., prompts/cues, time management, social and self-reward [23,27]). Those BCTs are delivered according to the need of the participant. The inclusion of additional BCTs should ensure that all delivered BCTs are identified and documented.

All the BCT definitions and practical examples for PA promotion are gathered in an online manual. The online manual includes information on the optimal timing to deliver the BCT as well as information on what theoretical domains are mainly influenced by the BCT [50,51]. BCTs are explained according to the V1 taxonomy by Michie et al. [21]. To simplify documentation, the BCTs subcategories of *social support* (i.e., *unspecified*, *practical*, and *emotional*) are merged. Similarly, two BCTs of *natural consequences* (*salience of consequences* and *information about emotional consequences*) and four BCTs of *reward and threat (social reward, social incentive, self-incentive*, and *self-reward)* are merged. The BCTs *time management* and *provide information on where and when to perform* are defined according to CALO-RE taxonomy [48].

The Movingcall program further comprises exercise science based advice for previously inactive adults. This includes information on a reasonable initial regime and increasing endurance and resistance training with regard to frequency, duration and intensity (e.g., start with 30 minutes brisk walking and increase to 45 minutes within the next three weeks). Further topics are the inclusion of PA in everyday life (e.g., plan walking distances, go to work by bike, balance training in the office), advice regarding balance training as well as stretching, and recommendations regarding movement or sports (e.g., interval training for Nordic walking). This information is gathered in our written guidelines.

### 2.6. Intervention Delivery

#### 2.6.1. Tailoring

Intervention content of all study arms is tailored individually to participants’ preferences and needs. This includes tailoring on demographics (e.g., age, place of residence), on the current behavior (e.g., form of activities, amount of PA per week), and on theoretical domains that influence the behavior (e.g., social support). Furthermore, information about participants’ intention, planning, pros and cons, self-efficacy, barriers, coping strategies, social support, knowledge on PA recommendation, PA behavior, personal goals and constraints, and current living conditions are used for tailoring. The required information is retrieved during the pre-test period. A focus is placed on BCTs that influence theoretical domains with the most potential for development. Depending on the study arm, the tailoring will be continued dynamically during the coaching process.

#### 2.6.2. Activity Profile

Participants in all study arms (including the control group) have access to their personal activity-profile on an interactive homepage (www.movingcall.com; Figure 2) [52]. The platform is designed to enable and standardize the delivery of the BCTs *action planning* and *self-monitoring*. The password-protected profiles can be used as a stand-alone tool or can simplify the interaction between participant and coach. To actualize the coaching process, each coach has access to the profile of the corresponding participant. Within the profile physical activities are scheduled and documented on a “plan page”. Activities can be selected from a database and entered into the participants’ plan. In order to self-monitor the PA behavior, completed activities need to be checked and additional activities should be entered. Participants are encouraged to document all activities lasting 10 minutes or more. The homepage provides kilocalories (kcal) and the metabolic equivalent (MET) of entered PA according to the compendium [53]. The profile further includes a note board to simplify communication between coach and participant. Interaction with other participants is not possible. Lastly, the homepage includes an online questionnaire tool. Participants use their login to answer the questionnaires and the coaches can access to the answers. The use of the profile is explained to all participants by phone prior to the start of the intervention. Participants are given access to their profiles during the intervention and during the follow-up period.

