## 2. Materials and Methods 

### 2.1. Study Design

Movingcall is conceptualized as a three-arm randomized controlled trial (Figure 1). The three study arms differ in terms of the delivery mode of the intervention: A “control group” received a single written recommendation at the beginning of the intervention (minimal intervention). A “coaching group” received 12 biweekly telephone coaching sessions. A “coaching and SMS group”, similarly received 12 biweekly telephone coaching sessions which were extended by two SMS messages per week. Data assessment took place at baseline, at the end of the six-month intervention, and after a six-month follow-up period without contact with the participants. The study was conducted at the Department of Sport, Exercise, and Health at the University of Basel, Switzerland.

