#### 2.7.1. Self-Reported Physical Activity

A structured telephone interview is carried out to assess participants’ self-reported PA. This interview follows the questions described in the SIMPAQ (Simple Physical Activity Questionnaire) [40]. In the present study, self-reported PA serves as the primary outcome. The SIMPAQ refers to PA during the previous 7 days. Furthermore, the structured interview asks for the time spent in bed and the time spent with the activities “sitting or lying”, “standing”, “walking”, and “other activities” (e.g., house work, gardening) for one of the usual days of the previous week. The duration and intensity of athletic training and recreational physical activities are assessed separately for each day. SIMPAQ was validated with university students by Schilling et al. [70] and has shown a moderate to strong correlation to accelerometer data and to established self-report questionnaires (Seven-Day Physical Activity Recall [71] and the short form of the International Physical Activity Questionnaire [72]). Compared to other self-report questionnaires the SIMPAQ is less time consuming [70]. 

In the present study, the original version of the SIMPAQ interview is extended to assess moderate or vigorous activities in everyday life. The intensity of the time spent walking and the time spent with other activities is specified by the question “how much of this time did you walk/move with an intensity that leaves you slightly out of breath?” Additional questions are added to the interview to assess: (1) If the last week is considered “a normal week”; (2) Illnesses and injuries during the last week; (3) Illnesses and injuries during the past 6 months including days of occupational absences; (4) Regular medication; and (5) Body weight including the time point and the location of weighing. In the post and follow-up tests two more questions are added to assess: (6) Other health-related behavior change attempts (e.g., stop smoking); and (7) The attendance to other services that support PA-related behavior changes (e.g., physiotherapy).

Interviews are conducted by specifically trained members of the study team. They are never conducted by the coach of a participant and interviewers are unaware of the group allocation.

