#### 2.7.2. ActiGraph Data

PA of 1 week is objectively assessed with the ActiGraph wGT3X-BT. The triaxial accelerometer records intensity and duration of accelerations and converts the signals to “activity counts” [55]. Participants receive the device by post at the beginning of the pre-, post-, and follow-up assessment period. All participants are requested to wear the ActiGraph on the non-dominant wrist for 7 to 10 consecutive days and nights. Hip-worn accelerometers are regarded as superior for predicting locomotion and estimating energy expenditure [73]. However, estimates of moderate and vigorous PA of wrist- and hip-worn accelerometers are comparable [74]. While hip-worn accelerometers are today’s standard, wrist-worn accelerometers have demonstrated higher wear-time compliance [74,75]. Wrist-worn assessment is therefore considered more feasible for the remote setting. 

Each participant is called by the allocated coach to explain how to handle the ActiGraph and the procedures of the test period. Participants are asked to wear the device until the SIMPAQ interview that is arranged after the requested wear time. The ActiGraph should be ignored and only removed when swimming or in a sauna. Non-wear periods are reported on a sheet enclosed in the mail. A prepaid envelope is attached for returning the ActiGraph along with the sheet.

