#### 2.7.3. Psychosocial Determinants of PA and other Measures

Online questionnaires are used to assess additional secondary outcomes and information needed for individual tailoring. Questionnaires are programmed within the interactive homepage. A link to answer the questionnaires is sent to the participant by e-mail. 

Applied instruments have previously been used in empirical research in German speaking countries. Except for self-composed items, acceptable validity and reliability have been demonstrated in previous studies (references listed below).

The following measures are assessed in the pre- post- and follow-up test-periods.

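### At 6 and 12 months the participant's own unblinded coach makes the ActiGraph call and can read the outcome questionnaires, which creates a risk of differential reactivity and reporting between coached and control arms

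*Protocol article*

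**What the plan says.** The plan takes care to separate coach and assessor for the primary outcome. Of the SIMPAQ interviews, section 2.7.1 says: "They are never conducted by the coach of a participant and interviewers are unaware of the group allocation".

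For the other outcomes the coach is present in two ways.

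- **ActiGraph.** Section 2.7.2 says: "Participants receive the device by post at the beginning of the pre-, post-, and follow-up assessment period". It then says: "Each participant is called by the allocated coach to explain how to handle the ActiGraph and the procedures of the test period". Nothing limits the call to the pre-test.
- **Questionnaires.** Section 2.7.3 says: "Online questionnaires are used to assess additional secondary outcomes and information needed for individual tailoring", and "Questionnaires are programmed within the interactive homepage". Of the psychosocial determinants, exhaustion symptoms and quality of life it says: "The following measures are assessed in the pre- post- and follow-up test-periods". Section 2.6.2 says of the same homepage: "Participants use their login to answer the questionnaires and the coaches can access to the answers". It draws no line between tailoring items and outcomes, or between pre-test and later answers.

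**The concern.** Contact with a coach is the treatment under test. If the treating coach telephones at the start of the week in which activity is measured, a coached participant may be more active in that week, or wear the device more diligently, in a way that a control participant would not. A coached participant who believes that the coach will read the answers may also report planning, self-efficacy or well-being more favourably.

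Three results are at stake:

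- the coached-versus-control comparison on the ActiGraph, which the Discussion relies on to counter social desirability and recall bias;
- the same comparison on the questionnaire outcomes;
- the mediation analysis in the third research question, which uses those questionnaires as mediators.

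**Working it through.** The document gives no figure from which a bias could be calculated, so the check sets its statements side by side.

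1. **Does the coach know the allocation?** Not at baseline: section 2.4 says that neither team nor participant knew it before the intervention began. At 6 and 12 months, yes. Coaches deliver the calls (2.6.3), write and send the SMS (2.6.4) and write the control arm's recommendation (2.6.7).

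2. **Does the contact differ by arm?** The call is nominally the same in every arm. The caller's relationship to the participant is not. In the coached arms it is the one coach who held 12 sessions (2.6.3). A control participant received one written recommendation and otherwise had study-team contact only at data assessments (2.6.7).

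3. **Is there a stated need for coach access to later answers?** Section 2.6.1 takes the information required for tailoring from the pre-test, and later tailoring happens within the coaching itself. No purpose is given for coach access to post-test or follow-up outcome answers.

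4. **Can the call reach the primary outcome?** The inputs are:
   - SIMPAQ recall: the 7 days before the interview (2.7.1).
   - Wear time: 7 to 10 consecutive days, with the device kept on until the interview, which is arranged after the requested wear time (2.7.2).

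   If the device is worn for w days up to the interview, with w between 7 and 10, the recall covers the last 7 of those days. The part of the wear period outside the recall is w − 7, that is 0 to 3 days. When these instructions are followed, all 7 recall days fall inside the wear period. An instruction call made at or before the start of wear therefore precedes both measures. A blinded interviewer prevents the interviewer from influencing the answers. Blinding cannot undo a real change in behaviour during the week being recalled. Such a change would move SIMPAQ and ActiGraph together, so agreement between them would not rule it out.

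5. **Which comparisons are exposed?**

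| Comparison | Exposed to this route? |
|---|---|
| Any arm at baseline | Not evidently: allocation unknown |
| Coaching vs coaching + SMS | Not evidently: same coach relationship in both |
| Either coached arm vs control, ActiGraph, 6 and 12 months | Yes: reactivity |
| Either coached arm vs control, questionnaires, 6 and 12 months | Yes, if participants know or suspect coach access |
| Either coached arm vs control, SIMPAQ, 6 and 12 months | Not through the interviewer; possibly through reactivity in the shared week |

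**The case against.** The strongest reply is that the coach measures nothing. The coach explains a device and can open a page. Questionnaires are self-completed online, activity minutes come from software, and controls get the same call. This stands, and it rules out any claim that the coach assesses or scores outcomes. It does not remove the two remaining routes, which run through the participant's behaviour and reporting.

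A second reply is that access rights for each questionnaire are operational detail that a condensed article may omit, and that the access sentence sits in the section on intervention delivery. This has some force, so the questionnaire part is the weaker half. The article also does not say whether participants know of the access. The ActiGraph call rests on an explicit statement.

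Several stronger readings are tempting, and the document does not support them:

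- **That the results are biased towards coaching.** The direction is plausible, but neither direction nor size is shown.
- **That the 12-month call breaks the no-contact period.** Section 2.1 places that assessment "after a six-month follow-up period without contact with the participants", so assessment contact comes after the period. The interview is such a contact too. Only the choice of caller is at issue.
- **That the rating of the coach relationship is biased against control.** It is asked only in the two coached arms, so there is no control comparison to distort.
- **That the shift is some fraction of the planned d = 0.21.** That effect was set for self-reported activity. No shift is given anywhere, and no planned effect is given for the ActiGraph or the questionnaires.
- **That every coached participant is affected at both later assessments.** Arm sizes are not stated, and 15–20% dropout is expected.

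**Conclusion.** The point holds as a risk of differential reactivity (ActiGraph week) and differential reporting (questionnaires) between the coached arms and control at 6 and 12 months. It plausibly favours the coached arms. Its size is unknown and cannot be estimated from the document. The primary outcome is protected from interviewer bias but not from reactivity in the week that it shares with the device.

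This rests on three assumptions:

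- the coach's call is repeated at post-test and follow-up, as the unrestricted wording implies;
- it comes at or before the start of wear, as its purpose implies, although no day is given;
- for the questionnaires, participants know or suspect that the coach can read their answers.

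It is a weakness that can be avoided cheaply, and it does not invalidate the design.

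**What to change.** For the 6- and 12-month assessments:

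- Have an existing team member who is not the participant's coach make the ActiGraph and test-period call. Preferably this is also not that participant's SIMPAQ interviewer, because a further conversation gives the participant another chance to reveal the allocation.
- Limit coach access on the homepage to the pre-test tailoring questionnaires.
- Tell participants that their coach will not see post-test and follow-up answers.

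The cost is some rescheduling of calls within the existing team, one platform permission, and a less familiar caller for coached participants.

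The Abstract and section 2.1 describe the assessments in the past tense, so they may already be complete. In that case, report who made the calls and who had access to the answers, add this to the limitations (the Discussion does not mention it), and interpret the coached-versus-control ActiGraph and questionnaire results with caution. Agreement between SIMPAQ and ActiGraph should not be presented as excluding reactivity.
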